#### Interim analysis

There are no planned interim analyses for the trial or stopping guidelines. There will, however, be an internal pilot study from which the data will contribute to the final analyses. The primary reason for this pilot study will be to check the assumptions about recruitment and feasibility of the trial. The DMEC and TSC will review the pilot data and recommend whether any changes are required to the trial team and whether the trial should continue or not. Furthermore, as we did not have data on the standard deviation of our primary outcome at one year, we will estimate this for the patients recruited into the internal pilot study. This will inform the potential need to increase the planned sample size as recommended by the independent DMEC.

### Cost-effectiveness analysis

The economic evaluation will assess the relative cost-effectiveness of surgical fixation compared with plaster cast treatment. Costs and health outcomes associated with the interventions will be collected during the 1-year trial period. However, the trial data is unlikely to provide all the evidence to inform the decision on whether surgical treatment represents a cost-effective option to the NHS. Therefore, these costs and outcomes will be extrapolated and modelled over a longer time horizon than captured by the trial (e.g. lifetime of the patient) if this is appropriate given the results of the trial. The additional data from the 5-year follow-up review on the long-term consequences of cast immobilisation and internal fixation, which are not adequately captured in RCTs, will be used to update the model results once available.

Detailed information will be collected on the costs of surgical fixation, including time in theatre, drugs and hospital bed usage, and the costs associated with plaster cast treatment. The impact of the two treatments on subsequent morbidity costs will be assessed. The use of hospital readmissions, outpatient attendances, general practice, community and personal health services will be collected during the various follow-up points through administered questionnaires. The primary perspective of the analysis will be that of the NHS and Personal Social Services, consistent with that used by the National Institute for Health and Care Excellence [58]. Private expenditures related to treatment will also be recorded and these costs will be included in a secondary analysis.

Health outcomes will be expressed in terms of the quality-adjusted life year (QALY) using the EQ-5D data collected at baseline, 6, 12, 26, and 52 weeks follow-up. The EQ-5D scores will be converted into QALYs using area under the curve analysis [59].

Cost and QALY data will be synthesised to generate an incremental cost effectiveness ratio (ICER) [60]. Multivariable regression analyses will be used to assess heterogeneity in costs, QALYs and cost effectiveness.

The 5-year follow-up review will facilitate an additional analysis that examines the relationship between outcomes reported at 1 year and 5 years. If considered appropriate, structural equation modelling [61] will be used to determine the factors that predict outcomes at 5 years and to assess the predictive performance of outcomes at 1-year. This may also be used to assess the cost-effectiveness of following patients up at 5 years post-surgery in general practice.

### Qualitative study of patient experience

The qualitative data collected in the nested study will be used to generate a model (or models) which reflect patient experiences of wrist fracture and treatment, and which identify difficulties and advantages of the different treatment options. Such models are likely to focus upon personal and lifestyle attributes as well as physical recovery, and to incorporate a range of non-clinical factors which are not routinely considered in clinical interactions. Insight into participation in a clinical trial will also be generated.

Sampling to the nested qualitative study will be purposive to include men and women from different trial sites, of different ages, occupations and leisure/sporting activities, and those with scaphoid fractures on their dominant and non-dominant sides. The sample will be drawn primarily from those individuals recruited to the trial (n to be determined by concerns for data saturation, see below). In addition, up to ten individuals who decline participation in the trial will be interviewed to explore their experience of fracture and their reasons for not taking part in the RCT. All participants will be interviewed within 6 weeks of their treatment and those in the trial will be interviewed again following collection of clinical and other data at the primary end-point (52 weeks).

All interviews will be semi-structured with open questions used to guide a discussion of a patient’s experience of treatment, their opinions about treatment benefits and drawbacks, their reflections upon wrist fracture and recovery, and their attitudes towards participating in clinical research. All interviews will be digitally recorded and transcribed in full.

Following the conventions of the constant comparative method, [62, 63] data analysis will be carried out alongside data collection, with interviews transcribed and analysed in batches before further data are collected. In this way, the process is iterative with models and theories developed from ‘within’ the interviews rather than from existing theory or clinical practice and tested or refined in the collection of more data.

These models will be further tested and *constantly* refined as new data are considered. Data collection, and analysis, ceases when no new themes or ideas are present in the interview data, and when the model of patient experience is stable and no longer growing or evolving. This point is known as data saturation [64], previous research suggests that this is often reached with as few as 10–13 interviews [65] – we are conducting around 40 interviews to include at least 15 from each treatment arm to enable data saturation. Data from those individuals not in the main trial will be considered alongside this data, and considered separately to inform practical concerns of trial recruitment.

Within this study we would expect to generate up to 4 interrelated models of patient experience: i) reporting patients’ experiences of wrist fracture, its impact upon their lifestyle, everyday functioning and their recovery; ii) reporting the benefits and difficulties associated with surgical fixation; iii) reporting the benefits and difficulties associated with plaster cast treatment and, iv) reporting experiences and attitudes towards involvement in surgical, clinical research.

### Adverse event management

Adverse events (AEs) related to the scaphoid fracture injury and its treatment during the 12 months after randomisation will be recorded by site Investigators and the categorisation of causality and expectedness confirmed by the Chief Investigator. AEs that may be expected with this injury to the wrist or a consequence of the trial treatments that do not need to be reported to the Research Ethics Committee (REC) include infection, delayed wound healing, CRPS, nerve or vessel events, screw related complications, fracture of scaphoid tuberosity, and chondrolysis. There are also adverse events specific to the plaster cast which are expected and do not need reporting to REC: soft cast/broken cast that leads to movement of wrist, pressure sores, CRPS, nerve compression, or pain due to tight cast. Movement in a cast is an untoward event as it can mean the fracture is not properly immobilised which can result in failure of the fracture to unite.

Serious adverse events that are confirmed to be *related* to the research and are *unexpected* will be reported to REC. All AEs will be routinely reported to the TMG, DMEC, and Sponsor. The DMEC will be responsible for reviewing related *and* unexpected serious adverse events.

All AEs that are unresolved at initial reporting will be reviewed by the Chief Investigator a month later to ensure that adequate action has been taken and progress made to manage the adverse event. Additional reviews at one month intervals will be conducted when necessary until the Chief Investigator decides that no further reporting is required.

The Chief Investigator will also be informed, by the reviewers of the X-rays/CT scans collected for the study, of any abnormalities identified. The Chief Investigator will judge whether the abnormality is clinically important and could impact on patient safety (e.g. a protruding screw). The need to notify the Principal Investigator of the site, and whether to record this as an AE, will also be considered. No actions or treatments will be discussed between the Investigators.

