### Complications

Expected and unexpected complications will be recorded at the 6, 12 and 52 week visit. The expected complications include:Infection, defined as for the “Surgical Site Infection” audit [52].Delayed wound healing, defined as any wound that has not healed by two weeks.Complex Regional Pain Syndrome (CRPS), defined as puffy painful swelling of the whole hand restricting full tuck of the fingers at 2 weeks.Nerve events (hypoaesthesia or numbness in the territory of the palmar cutaneous branch of the median nerve, superficial division of the radial nerve or the median nerve).Vessel events (large (>2 cm) haematoma in the line of the radial artery).Screw related complications (protrusion of either end into the adjacent joint, fracture or bending of the screw, a radiolucent halo around any part of the screw > 1 mm, screw backing out or moving).Degenerative change in the adjacent joints [53].Avascular necrosis (AVN) of the proximal pole of the scaphoid.

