### Randomisation

The Research Nurse will identify potentially eligible patients presenting in Accident and Emergency (A&E) Departments, or referred from various sources (e.g. walk-in centre, cottage hospital), and at fracture clinics. The orthopaedic surgeon will confirm eligibility and invite the patient to consider joining the study. The Research Nurse or clinician will then provide an information sheet and answer any questions. The patient will be asked whether they agree to consent at that time or are offered up to 48 h to discuss the study and their participation with family or friends before deciding.

When patients have given consent their baseline forms will be completed and randomisation done. The Research Nurse or recruiting clinician will contact York Trials Unit, either by telephone or via the internet, to access the secure randomisation service. This will ensure treatment concealment and unbiased allocation. Once eligibility is confirmed, patients will be randomised (via a secure, computer generated allocation sequence) to receive immediate surgical fixation or immobilisation of the wrist in a cast.

Patients and their clinician will be informed of the allocations. As the trial is pragmatic and compares surgery with initial cast treatment, blinding of participants and clinicians to treatment allocation is not possible. When possible, the surgeon will take no part in the postoperative subjective assessment of patients. The statistical analysis will also be performed blind as far as possible. We will mitigate against bias by ensuring that all radiographs and CT scans are assessed by two independent consultant musculoskeletal radiologists and a consultant orthopaedic surgeon.

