The impact of missing PRWE outcome data will be minimised to some extent by using the mixed model, which allows the inclusion of intermittent responders in the primary analysis. PRWE scores for complete and intermittent responders will be compared descriptively. The impact of missing data will additionally be assessed using multiple imputation by chained equations. Missing outcome and covariate data will be predicted by age, fracture displacement, hand dominance, available PRWE data at other follow-up time points, and any baseline covariates found to be predictive of missing 12 month outcome data.

All secondary outcomes will be summarised descriptively. The following outcomes will be analysed using the same methods as the primary analysis adjusting for the same covariates: pain and disability subscales of the PRWE, physical health and mental health component summaries of the SF-12 and range and grip strength. Where available, baseline values of the dependent variable will also be included as a covariate in the models. The presence of any complication assessed by clinical examination up to 52 weeks will be analysed by logistic regression (sufficient numbers permitting). Complications will be defined as medical, surgical or plaster cast related. Union will be assessed as a percentage (0–100 %) and categorised as: total non-union [0 %]; slight union [>0–20]; partial union [>20–70]; mostly united [>70–<100]; and complete union [100 %]. Summary statistics for union will be presented at each time point by trial arm. Union will be dichotomised into a ‘Probably need surgery’ group [0–20 %] and a ‘Probably do not need surgery’ group [>20–100 %] and analysed using a logistic regression adjusting for treatment group.

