Two subgroup analyses will be undertaken: one exploring patient preferences (surgery, plaster cast, no preference) and the second exploring the type of fracture displacement (undisplaced, displaced), for any differential effect of the trial treatments in these subgroups. Each baseline factor (preference or displacement) and its interaction with the randomised treatment group will be added to the primary analysis model. Our expectation is for patients who preferred surgery to benefit more from surgery over plaster cast treatment and conversely for patients who preferred plaster cast to benefit more from plaster cast than surgery. For patients with a displaced fracture we expect them to benefit more following surgery than patients whose fracture is undisplaced. Since the trial is not powered for these subgroup analyses, any inferences will be made with caution.

The number of adverse events experienced by each participant and the total number of events overall will be summarised for each treatment group.

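### Sites record an adverse event only if they judge it related to the injury or its treatment, so some serious events can go unrecorded, possibly unequally by arm

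*Protocol article*

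**What the plan says.** Under Adverse event management, the recording rule is: "Adverse events (AEs) related to the scaphoid fracture injury and its treatment during the 12 months after randomisation will be recorded by site Investigators". The same sentence continues with "the categorisation of causality and expectedness confirmed by the Chief Investigator". Onward reporting follows from this record: "All AEs will be routinely reported to the TMG, DMEC, and Sponsor". Reporting to the ethics committee, and the DMEC's specific review duty, concern serious events that are both related and unexpected.

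The Statistical analysis plan section uses the record as follows: "The number of adverse events experienced by each participant and the total number of events overall will be summarised for each treatment group". On who makes the first judgement, the Randomisation section says "blinding of participants and clinicians to treatment allocation is not possible".

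Two other routes bear on harms:

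- **Complications.** "Expected and unexpected complications will be recorded at the 6, 12 and 52 week visit". The analysis is stated as "The presence of any complication assessed by clinical examination up to 52 weeks will be analysed by logistic regression", if numbers are sufficient, and complications are classed as medical, surgical or cast related.
- **Imaging.** "The Chief Investigator will also be informed, by the reviewers of the X-rays/CT scans collected for the study, of any abnormalities identified". The Chief Investigator then considers whether the finding should be recorded as an adverse event.

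**The concern.** Causality is normally assessed after an event has been recorded. Here a causal judgement decides whether the event is recorded at all. A site that wrongly regards a serious event as unrelated has no stated duty to enter it, so the Chief Investigator's confirmation of causality does not reach it through the site route. An example is a systemic illness some weeks after an operation.

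The judgement is made with knowledge of allocation, and the arms are not alike in what could be attributed. Every patient in the surgery arm is planned to have an operation. In the cast arm only those whose fracture fails to unite are, which the protocol puts at 10 to 12%. Errors in judging relatedness therefore need not balance.

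This matters because the Sample size section says surgery has to justify its added cost and exposure to risk. The Interim analysis section gives no stopping guidelines, so the DMEC relies on the completeness of what it is sent.

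**Working it through.** The protocol gives no adverse event rate and no rate of misjudged relatedness, so the check is mainly a reading of the sections side by side.

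**Step 1: follow a serious event that the site judges unrelated.**

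| Stage | Section | Is the event captured? |
|---|---|---|
| Site adverse event record | Adverse event management | No; recording is confined to events related to the injury and its treatment |
| Causality confirmed centrally | Adverse event management | Not through this route; it was never submitted |
| Reports to TMG, DMEC and Sponsor | Adverse event management | No; in effect these are all recorded events |
| DMEC review and ethics reporting of serious events | Adverse event management | No; both require relatedness |
| Summary by arm | Statistical analysis plan | No; it counts recorded events |

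**Step 2: see which other routes could pick it up.**

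- *Complications at 6, 12 and 52 weeks.* No relatedness condition is stated, unexpected complications are included, and the analysis has a medical category. This route can capture some events that the adverse event record misses. Its limits are these: the listed expected complications are all local to the injured limb. The analysed outcome is the presence of any complication found on clinical examination, which is not a count of serious events from all causes. No hospital attendance is required at 26 weeks, so scheduled clinic capture has a gap of 52 − 12 = 40 weeks. Whether a systemic illness counts as a complication probably also needs a local view of its cause.
- *Imaging.* This route can add an adverse event without any site judgement, but only for what radiographs or CT show.
- *Resource-use questionnaires.* The Cost-effectiveness analysis section collects hospital readmissions and outpatient attendances. They are collected for costing, and no link to the adverse event record is stated.

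**Step 3: what remains.** The gap is the set of events that are off the complication list, not visible on imaging, not noted as a complication at a visit and judged unrelated by the site. The number of such events cannot be derived from the protocol.

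**Step 4: cost of closing the gap.** Let the proportion of patients with a serious event in 12 months be p. The protocol gives no value, so p is assumed to lie between 2% and 5%, with one form per patient.

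- Forms = 438 × p
- p = 0.02: 438 × 0.02 = 8.76, about 9
- p = 0.05: 438 × 0.05 = 21.9, about 22

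This is an assumed total of serious events, and so an upper limit on additional forms, because related serious events are recorded already. It measures workload; it does not estimate bias.

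**The case against.** The strongest reply is that the protocol does not depend on this one record. Complications, including unexpected ones, are recorded at three visits with no stated relatedness test and are compared between arms. Independent readers report image abnormalities to the Chief Investigator, which can lead to an adverse event being added. The DMEC has access to the unblinded comparative data. The entry condition covers the injury as well as the treatment, so a site need not attribute an event to surgery to record it. The article may also condense a fuller safety section, and it mentions a Trial Site Manual that is not shown.

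Much of this stands, and it rules out a stronger reading. A reader might infer that the central causality check can only remove events, and that missed harms never reach the DMEC or any comparison by arm. The documents do not support that. The imaging route can add events, nothing says that an event the Chief Investigator reclassifies is deleted, and the complication analysis is itself a comparison by arm.

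The reply does not remove the point. The recording rule is stated outright, so the point does not rest on a gap left by a condensed article. The other routes are limited by body site, by what imaging shows, or by what is noted at a visit. None is a record of serious events from all causes.

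**Conclusion.** The point holds in a narrow form. As written, the rule lets a serious event go missing from the adverse event record, and from the DMEC reports and summary by arm that draw on it, when an unblinded site judges it unrelated and neither the complication route nor the imaging route picks it up. That loss could differ by arm. Whether it would be large or small cannot be said from the protocol. A reader might take the figure of 9 to 22 as the number of events at risk of loss, but it is only a ceiling on extra forms under an assumed rate of 2% to 5%. The conclusion assumes that no fuller safety document already requires recording of serious events from all causes. The change is worth making because it is cheap and removes a filter that may depend on the arm; nothing here shows that the planned safety comparison is wrong.

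**What to change.** In Adverse event management, keep the present recording of all adverse events related to the injury or its treatment. Add that sites record every serious adverse event in the 12 months after randomisation, whatever their own view of its cause, and that the Chief Investigator then categorises causality. The addition must not replace the present rule, or non-serious treatment-related events that are recorded now would be lost. Leave the ethics committee reporting rule (related and unexpected) as it is.

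In the Statistical analysis plan section, state that serious events will be summarised by arm twice: from all causes, and those categorised as related. The first count does not depend on anyone's judgement of cause.

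The cost is a short wording change, one further summary and a small number of serious event forms: at most about 9 to 22 under the assumption above, and fewer in practice.

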### Quality control

The University Hospitals of Leicester NHS Trust will be the Sponsor for this project. This study will be fully compliant with the Research Governance Framework and Medical Research Council Good Clinical Practice Guidance. If a patient wishes to complain formally, they will be advised to do this through the usual NHS Complaints Procedure. If a patient is harmed and this is due to someone’s negligence then they may have grounds for legal action or compensation against the Sponsor (in respect of harm arising out of participation in the trial) or the NHS (in respect of any harm which has resulted from the treatment received).

Review of core trial processes will be undertaken by the Trial Management Group (TMG) on a quarterly basis which includes representation from the Sponsor. These meetings focus on aspects of patient recruitment (e.g. enrolment, consent, eligibility); allocation to study groups; adherence of the trial interventions to the protocol; monitoring of adverse events and reasons for patient withdrawal; and retention of trial participants. When necessary the review will be undertaken at a recruiting site level and information feedback to the Principal Investigator and Research Nurses at each site. Independent review of the trial processes is undertaken every six months by the DMEC and TSC. These committees assist the TMG with their audit of trial processes and advise on strategies to preserve the integrity of the trial.

